#### **5.1.4 Criteria for Clinical Trial Suspension and Termination**

In case of any of the following circumstances, the clinical trial shall be suspended or terminated, and the investigator, the sponsor and the ethics committee shall jointly decide whether to terminate the clinical trial in advance:

- After vaccination, the number of subjects with adverse reactions with severity of Grade 3 exceeds 15% of the number of subjects vaccinated in this subgroup.
- One case of Grade 4 adverse reaction or SUSAR was confirmed to be related to vaccination.

In case of any of the following circumstances, the clinical trial shall be terminated:

- The Sponsor found that the vaccine has potential safety hazard, or the study has quality problems and requires the complete termination of the trial.
- The Ethics Committee requests termination of the trial because of the ethical violation in the study.
- The administrative authority requests termination of the trial.

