## LIST OF ABBREVIATIONS

|          |                                                    |
|----------|----------------------------------------------------|
| ACE2     | Angiotensin converting enzyme 2                    |
| ADE      | Antibody Dependence Enhancement                    |
| AE       | Adverse Event                                      |
| BP       | Blood Pressure                                     |
| CI       | Confidence Interval                                |
| COA      | Certificate of Analysis                            |
| CoV      | Coronavirus                                        |
| COVID-19 | Coronavirus disease of 2019                        |
| DNA      | Deoxyribonucleic acid                              |
| DSMB     | Data and Safety Monitoring Board                   |
| ECRF     | Electronic Case Report Form                        |
| EDC      | Electronic Data Capture System                     |
| EAC      | Endpoint Information Committee                     |
| FAS      | Full Analysis Set                                  |
| GCP      | Good Clinical Practice                             |
| GMP      | Good Manufacturing Practice                        |
| GMT      | Geometric Mean Titer                               |
| GMI      | Geometric mean increase                            |
| IB       | Investigator's Brochure                            |
| ICF      | Informed Content Form                              |
| IEC      | Independent Ethics Committee                       |
| MERS     | Middle East Response Syndrome                      |
| NMPA     | National Medical Products Administration           |
| MFAS     | Modified Full Analysis Set                         |
| PPS      | Per-Protocol Set                                   |
| PCR      | Polymerase Chain Reaction                          |
| RNA      | Ribonucleic acid                                   |
| SAE      | Serious Adverse Events                             |
| SARS     | Severe Acute Respiratory Syndrome                  |
| SOP      | Standard Operating Procedure                       |
| SS       | Safety Set                                         |
| SUSAR    | Suspected and Unexpected Serious Adverse Reactions |

|     |                           |
|-----|---------------------------|
| VED | Vaccine Enhanced Disease  |
| WHO | World Health Organization |

CONFIDENTIAL

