| Criteria for suspension and early termination | 
In case of any of the following circumstances, the trial shall be suspended, and the investigator, the sponsor and the Ethics Committee shall jointly hold a meeting to decide whether to terminate the clinical trial early:
 
 
- The number of subjects with adverse reactions of severity Grade 3 or above exceeds 15% of the subjects vaccinated in this subgroup;
 
- One case of Grade 4 adverse reaction related to vaccination or SUSAR has occurred.
 
 
In case of any of the following circumstances, the clinical trial shall be terminated early:
 
 
- Sponsor has found that the vaccine has potential safety hazards or the trial has quality related problems, and requiring the complete termination of the study.
 
- The Ethics Committee requests the termination of the trial because of the violation of ethics in the trial.
 
- Request by the administrative authority to terminate the trial.
 
 |
| Trial End point                               | 
Immunogenicity endpoint:
 
Primary endpoint:
 
GMT and the 4-fold rise of anti-SARS-CoV-2 neutralizing antibody 14 days after sequential vaccination of one booster dose;
 
GMT and 4-fold rise of anti- SARS-CoV-2 neutralizing antibody 28 days after sequential
                                                                                                                                                                                                                                                                                                                                                                                                                                                                                                                                                                                                                                                                                                                                                             |

vaccination of one booster dose.

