## 7.6 Criteria for Suspension or Early Termination

**In case of any of the following circumstances, the trial shall be suspended, and the investigator, the sponsor and the Ethics Committee shall jointly hold a meeting to decide whether to terminate the clinical trial early:**

- One case of Grade 4 adverse reaction related to vaccination or SUSAR in any group, including death or life-threatening SAE;
- The number of subjects with adverse reactions of severity Grade 3 or above

---

exceeds 15% of the subjects vaccinated in this subgroup;

- DSMB evaluation of clinical research has high potential safety risks.

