### **(2) Reporting Procedures for Serious Adverse Events**

- Reporting procedures of investigators

Any serious adverse event, whether or not related to the investigational vaccine, the

investigator must submit the initial report of the "Serious Adverse Event Report Form" to the drug administration department, the sponsor and the ethics committee by fax, e-mail or EDC system or personal delivery within 24 hours after learning about it.

Subsequently, the follow-up report of the "Serious Adverse Event Report Form" shall be submitted regularly until the end of the event. All information is reported in the "Serious Adverse Event Report Form" in the form of written reports, including description of adverse reactions/events, onset time and type, duration, intensity, causal relationship with vaccination, results, treatment methods (symptomatic treatment) and other relevant clinical and laboratory data.

When receiving the report of serious adverse events/reactions, the investigator shall, together with the sponsor, comprehensively consider the duration, scope, intensity, outcome and the willingness of the subject to decide whether the subject should continue to participate in the study or withdraw from the study in advance.

- Reporting procedure of sponsors

During the clinical trial of drugs, sponsors need to quickly report unexpected and serious adverse reactions (SUSAR) that are definitely related to or suspicious of the tested drugs in the form of case-by-case safety reports according to the Standards and Procedures for Rapid Reporting of Safety Data during Clinical Trial of Drugs. If the researcher and the sponsor cannot reach an agreement on the judgment of the causal relationship between adverse events and drugs, either party's judgment cannot exclude those related to the test drugs, and the sponsor should also make a quick report.

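### Section 5.1.4 asks for confirmed relatedness before a single Grade 4 reaction or SUSAR suspends the trial; the synopsis and section 7.6 do not ask this of a SUSAR, and no list is said to govern

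*Protocol*

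**What the plan says.** The suspension criteria stand in three places in the protocol.

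- **Synopsis, row on suspension and early termination.** Two triggers. The one-case trigger is "One case of Grade 4 adverse reaction related to vaccination or SUSAR has occurred". The percentage trigger is "The number of subjects with adverse reactions of severity Grade 3 or above exceeds 15% of the subjects vaccinated in this subgroup".
- **Section 5.1.4.** Two triggers. The one-case trigger is "One case of Grade 4 adverse reaction or SUSAR was confirmed to be related to vaccination". The percentage trigger is worded as "the number of subjects with adverse reactions with severity of Grade 3 exceeds 15" per cent of those vaccinated in the subgroup, with no mention of higher grades.
- **Section 7.6.** Three triggers. The one-case trigger is "One case of Grade 4 adverse reaction related to vaccination or SUSAR in any group, including death or life-threatening SAE". The percentage trigger again covers Grade 3 and higher. The third is "DSMB evaluation of clinical research has high potential safety risks".

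Two other places fix what a SUSAR is. The list of abbreviations expands it as "Suspected and Unexpected Serious Adverse Reactions". Section 8.3 (2) says that "sponsors need to quickly report unexpected and serious adverse reactions (SUSAR) that are definitely related to or suspicious of the tested drugs".

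The protocol contains no statement that one of the three lists takes precedence, and 5.1.4 does not refer to 7.6.

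**The concern.** The one-case rule is the fastest safety brake in this trial, and it is written with two thresholds. In 5.1.4 the requirement of confirmed relatedness covers both the Grade 4 reaction and the SUSAR. On the natural reading of the synopsis and 7.6, relatedness qualifies the Grade 4 reaction, while a SUSAR suspends the trial as soon as it occurs.

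The word *confirmed* has practical force here because the protocol describes steps at which causality is settled later. Under 8.3, doubtful causality goes to an expert meeting, and compensation depends on confirmation by an expert investigation team. A reader of 5.1.4 could reasonably take such a step to be what is meant and keep vaccinating until it is complete. Screening and vaccination both take place at D0 (section 7.2.1), so new subjects could be dosed in the meantime.

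**Working it through.** No sample-size, power or alpha figure is at issue. The check is a comparison of the three lists, followed by a short calculation on whether the percentage rule could stand in for a delayed one-case pause.

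**Step 1. Compare the lists.**

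| Element | Synopsis | 5.1.4 | 7.6 |
|---|---|---|---|
| Number of suspension triggers | 2 | 2 | 3 |
| One SUSAR, relation suspected | suspends | not met until relation is confirmed | suspends |
| One Grade 4 reaction | must be related | must be confirmed as related | must be related |
| 15% rule counts | Grade 3 and higher | Grade 3, as written | Grade 3 and higher |
| DSMB trigger | absent | absent | present |
| Immediate action | suspend, then meet on termination | suspend or terminate, then joint decision | suspend, then meet on termination |

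**Step 2. Does a SUSAR already imply confirmation?** No. The abbreviation list calls it suspected. Section 8.3 (2) covers both definite and suspected relations, and requires expedited reporting even when investigator and sponsor disagree on causality, provided one of them cannot exclude a relation. A SUSAR can therefore exist while causality is open, and 5.1.4 adds a condition that the definition does not contain.

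**Step 3. Test case.** Take one SUSAR whose relation is suspected and still under discussion. It meets the trigger in the synopsis and in 7.6. It does not meet the trigger in 5.1.4 as written.

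**Step 4. Would the percentage rule catch a delayed pause?** The term *subgroup* is not defined, so both plausible readings are shown, at full enrolment.

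- One sequential vaccine group of 300 (Table 1): 0.15 × 300 = 45. The rule requires more than 15%, so at least 46 subjects (46/300 = 15.3%).
- One timing cohort of 600 (section 10.1): 0.15 × 600 = 90, so at least 91 subjects (91/600 = 15.2%).

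The one-case trigger is met at 1/300 = 0.33% of a group. The percentage rule works on a different scale and would not replace a delayed one-case pause.

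**Step 5. The other differences.** Grade 3 against Grade 3 and higher has little effect when the lists are read together, because one related Grade 4 reaction already suspends the trial. Read literally and alone, however, 5.1.4 counts an unconfirmed Grade 4 reaction under neither of its triggers. The DSMB trigger appears only in 7.6. The wording on suspension or termination in 5.1.4 leads to the same joint decision as in the other lists. These points are minor, and the same edit aligns them.

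**The case against.** The strongest reply is that the lists do not exclude one another. Each gives circumstances any one of which is sufficient, and 5.1.4 nowhere says that only a confirmed case counts. A protocol binds as a whole, so one unconfirmed SUSAR suspends the trial under the synopsis and 7.6 whatever 5.1.4 says. This stands. A reader might infer that 5.1.4 lets vaccination continue after an unconfirmed SUSAR, or that the three lists cannot all be obeyed. The text supports neither inference.

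Second, safeguards limit the harm. Under 8.3 (2) the investigator reports every SAE, related or not, to the drug authority, the sponsor and the ethics committee within 24 hours. Two of the three parties to the suspension decision are thus alerted before any confirmation. Section 5.1.4 also lets the sponsor end the trial over a potential safety hazard, with no confirmation wording. This stands too, but it shortens a delay rather than restoring an automatic pause.

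Third, *confirmed* may be loose wording for a relation that has been assessed. That is possible: 5.1.4 names no confirming body, standard or waiting period. Equally, a reader might equate it with the Definite category in 4.5.3, which requires recurrence on repeat use and so could not be met with one study dose. The document makes no such link, and the point does not rest on it. Whatever was intended, the plain wording sets a higher bar than the other two lists.

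**Conclusion.** The point holds as an inconsistency in a safety rule. Section 5.1.4 states the one-case trigger more strictly than the synopsis and 7.6, and no text settles which list applies. Read cumulatively, the protocol still requires suspension on a suspected SUSAR. The risk is that a site or committee working from 5.1.4 alone waits for confirmation and delays that pause.

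The difference affects a trigger that one subject meets. The number of subjects whom a delay would expose cannot be derived, because the protocol gives no vaccination rate. The counts of 46 and 91 rest on an assumed meaning of *subgroup* and on full enrolment, and show only that the percentage rule is no substitute. The conclusion assumes the natural reading of the synopsis and 7.6, in which a SUSAR needs no further qualification. Sample size and primary analysis are not touched. The text should be corrected because the change is cheap and protects subjects.

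**What to change.** Make section 7.6 the single governing list. Replace the suspension criteria in 5.1.4 and in the synopsis with a cross-reference to it. This removes the confirmation condition, applies the 15% rule to Grade 3 and higher throughout, makes the DSMB trigger visible from all three places, and fixes the order: suspend first, then decide jointly on termination. The wording of the 7.6 triggers, including its phrase on deaths and life-threatening events, can stay as it is; narrowing it is not needed to resolve this point.

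The cost is one wording amendment, in 5.1.4 and the synopsis, with a line in 7.6 stating that it governs. The downside is a possible temporary pause for a SUSAR later judged unrelated, which the synopsis and 7.6 already accept.

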## **6. PRODUCT INTRODUCTION**

### **6.1 Description and Characteristics of the Investigational Products**

Recombinant COVID-19 vaccine (CHO cells) is a recombinant protein expressed by recombinant Chinese hamster ovary (CHO) cells and designed based on the receptor binding domain (RBD) of S protein of SARS-CoV-2. Engineered cells were cultured, harvested and purified by a series of processes, and then added with aluminum hydroxide adjuvant.

This product is a sterile formulation, packed in vial with a specification of 0.5 ml/dose/vial. After shaking, it is an opalescent suspension, which can be layered due to precipitation and easily shaken away without lumps.

The main active ingredient of this product is the recombinant protein formed by the receptor

binding region of SARS-CoV-2 spike protein. Excipients include sodium chloride, aluminum hydroxide adjuvant, histidine, etc. Each dose contains 20µg of recombinant protein, 4.38 mg of sodium chloride, 0.39 mg of histidine, 0.30 mg of aluminum and water for injection. Used to prevent diseases caused by SARS-CoV-2.

### **6.1.1 Investigational Vaccine**

Investigational Vaccine: Recombinant COVID-19 Vaccine (CHO cell)

Manufacturers: Sinopharm CNBG National Vaccine and Serum Institute (NVSI),  
Lanzhou Institute of Biological Products Co., Ltd. (LIBP)

Specifications: 0.5 ml/vial per human use, which contains 20ug of viral protein antigen.

Storage Condition: 2-8 °C.

Vaccine Batch Number: 20201113

Expiry Date: Nov 11, 2022

Control vaccine: Inactivated COVID-19 Vaccine (Vero cell)

Manufacturer: Beijing Institute of Biological Products Co., Ltd.

Specifications: 0.5 ml/vial per human use, which contains 6.5U of antigen.

Storage conditions: 2-8 °C

Vaccine Batch Number: 2021071710.

Expiry Date: Jul 8, 2023

### **6.1.2 Production Process**

The recombinant COVID-19 vaccine (CHO cells) developed in this project takes CHO cells as the express system and SARS-CoV-2 spike protein as the target, applying genetic engineering technology to construct and screen stable cell lines with recombinant expression protein. After culture, harvesting and a series of purification processes and adding aluminum hydroxide adjuvant, the vaccine is finished after filling.

## **6.2 Vaccine Packaging and Labeling**

All investigational vaccines are packaged in doses in boxes with the same appearance and only marked by the vaccine number. Each study ID will be matched with a unique vaccine number, the format of the vaccine number is AE+4-digit Arabic number. See the following label for detailed information.

### 6.2.1 Vaccine Labeling

- (1) Each dose of vaccine is packaged separately and the vaccine number is stucked onto.
- (2) After the vaccine is put into use, the initials of the subject and the vaccination date shall be filled on the outer package.

#### Clinical Trial Labeling Illustration

##### Outer Packaging Box Label

|                                                |                          |           |           |           |
|------------------------------------------------|--------------------------|-----------|-----------|-----------|
| Recombinant COIVD-19 Vaccine (CHO cell) |                          |           |           |           |
| For Clinical Use Only                   |                          |           |           |           |
| Vaccine Number: AExxxx                  |                          |           |           |           |
| Initials:                               | Vaccination Date: | YY | MM | DD |
| Storage at 2-8°C, 0.5mL/dose            |                          |           |           |           |
| Batch Number:                           |                          |           |           |           |

##### Vaccine Label:

|                                               |
|-----------------------------------------------|
| Recombinant COVID-19 Vaccine(CHO cell) |
| (For Clinical Use Only)                |
| Vaccine Number: AExxxx                        |
| Batch Number: XXXX                            |

### 6.3 Vaccine Storage and Transportation

Vaccines should be stored and transported at 2 ~ 8 °C away from light to prevent freezing. The temperature during vaccine transportation and storage shall be dynamically monitored and recorded. If the storage and transportation temperature conditions exceed the specified range, the on-site investigators should immediately contact the personnel of the responsible clinical institutions and the sponsors to decide whether the vaccine can be used.

The management of receiving, keeping, formulation, recovery, returning/destroying of the investigational vaccine shall conform to the requirements of relevant laws and regulations.

#### 6.3.1 Vaccine Transportation

The whole process of vaccine management should meet the cold chain requirements, and there should be vaccine transportation and storage conditions that meet the requirements of the protocol. During the vaccine transportation, there should be a transportation sheet and temperature monitoring. Upon arrival, the packaging condition and unpacking temperature should be recorded. After the recipient receives the vaccines, the transportation sheet should be signed, faxed, or copied to the sender. Both parties should properly keep the transportation sheet.

### **6.3.2 Vaccine Storage and Distribution**

The investigational vaccines should be kept in a separate area, locked in dedicated cabinet and managed by dedicated personnel. Vaccine recipient must verify and record the batch number, expiration period and delivery status of vaccines, establish work forms for vaccine handover, registration, use and recovery, fill in them as required, and keep them in the work records.

The trial vaccine shall not be used in non-clinical trial population.

### **6.3.3 Vaccine Records**

*Vaccine handover records:* The sponsor will provide investigational vaccines, control vaccines (placebo) and vaccine handover sheet, and investigator will verify the name, batch number and quantity of the vaccine upon receiving.

*Vaccine registration and use records:* the investigator shall establish vaccine registration and use records and distribute investigational vaccine and control vaccines according to the number of people in the observation groups.

*Vaccine recycle record:* The abandoned, expired and the remaining vaccines in this trial are returned to sponsor. Sponsor receives vaccines and verifies the batch number and quantity of vaccines, fills in the vaccine handover form, and makes relevant records, which are signed by vaccine manager and sponsor representatives

## **6.4 Administration and Immunization Schedule**

Route of Administration: lateral deltoid muscle of either upper arm, intramuscular injection.

Vaccination Procedure: Among the population who had completed two doses of inactivated COVID-19 vaccines according to the 0 and 21 days (+7 days) immunization schedule, one dose of recombinant COVID-19 vaccine (CHO cells) or inactivated COVID-19 vaccines (Vero cells) will be inoculated at different time points of 1~3 months, 4~6 months, and  $\geq 6$  months for sequential immunization

## 7. STUDY WORKFLOW AND VISITING METHOD

### 7.1 Schedule of Visits

Table 4 lists the assessment items and procedures according to the phase of the clinical studies and visit.

### 7.2 Study Procedure

#### 7.2.1 Screening Period, Baseline Period, and Vaccination Procedure (D0)

The first visit was conducted according to the following procedure and evaluation processes.

